## Abstract

**Background:**

Parkinson’s disease (PD) is a common neurodegenerative disease. No disease-modifying treatment is available, and therapy is symptomatic. The histopathologic hallmark is the loss of dopaminergic neurons and accumulation of α-synuclein (α-syn) in surviving neurons, but the underlying pathophysiology is unclear. Inflammatory mechanisms seem to play a prominent role, with an imbalance of immune functions and neurotoxicity caused by reactive oxygen species (ROS). Involvement of peripheral adaptive immunity, with an imbalance in T cell subpopulations and in the expression of transcriptional factors in CD4+ T cells, has also been reported. Although clinical presentation is defined by motor symptoms, patients also report non-motor symptoms, often before the onset of a clinically established disease. Etiopathogenesis of PD is unknown, but an initial aggregation of α-syn in the gut, with subsequent propagation along the vagus nerve to the brain has been hypothesised. Interestingly, in an α-syn overexpressing murine model, the absence of gut microbiota prevented both microglia activation and motor impairment, thus pointing to a fundamental role of microbiota in the development of PD. Magistrelli et al. showed that in peripheral blood mononuclear cells of PD patients, probiotics modulate the in vitro production of cytokines toward an anti-inflammatory profile and reduce the production of ROS.

**Methods:**

This is a pilot randomised placebo-controlled clinical trial protocol for a 12-week treatment with probiotics. At least 80 patients affected by PD will be recruited and randomly allocated to either the treatment or placebo group in a 1:1 ratio. General inclusion criteria will be the onset of PD 2 to 5 years before the trial and absence of autoimmune comorbidities or immunomodulating therapy. Our primary endpoint is the assessment of changes in extracellular cytokine levels (Interferon (IFN)-γ, tumour necrosis factor (TNF)-α, interleukin (IL)-4, and IL-10) and ROS production. Secondary outcomes include changes in lymphocyte subpopulations and transcriptional factors mRNA levels.

**Discussion:**

This study is designed to highlight the potential beneficial role of probiotics administration on peripheral immunity through the modulation of gut microbiota. Explorative outcomes will be evaluated to assess variations in motor and non-motor symptoms and the possible correlation with probiotics administration.

**Trial registration:**

ClinicalTrials.gov ID NCT05173701. Registered 08 November 2021

## Introduction

### Background and rationale

Parkinson’s disease (PD) is a common neurodegenerative disease, affecting up to 1–2 people in 1000. Prevalence increases with age and is estimated at 1% in people over 65 [1]. No treatment which prevents PD onset or delays its progression is yet available, and therapy is focused on the symptom management through dopamine supplementation and the use of direct and indirect dopaminergic agents [2]. The histopathologic hallmark of PD is the loss of dopaminergic neurons and accumulation of α-synuclein (α-syn) in surviving neurons, but the underlying pathophysiology is still unclear [3]. Inflammatory mechanisms have been suggested to play a prominent role in the development of the disease [4], with an imbalance of immune functions, as well as neurotoxicity caused by reactive oxygen species (ROS) [5, 6].

Further evidence highlights the involvement of peripheral adaptive immunity in PD [7, 8], reporting an imbalance in T cell subpopulations and in the expression of transcriptional factors in CD4+ T cells [9] in PD patients and in subjects with REM sleep behaviour disorder, which is considered a potential prodromal state in the development of PD [10]. Although clinical presentation is defined by the presence of motor symptoms such as bradykinesia, rest tremor, and rigidity, patients often also report non-motor symptoms including hyposmia, constipation, pain, anxiety, and depression that may precede the onset of a clinically established disease [11, 12].

Etiopathogenesis of PD is unknown, but work by Braak et al. hypothesised an initial aggregation of α-syn in the gut with subsequent propagation along the vagus nerve to the brain, finally reaching the substantia nigra in the mesencephalon [13].

Interestingly, in an α-syn overexpressing murine model of PD, the absence of gut microbiota prevented both microglia activation and motor impairment [14], thus pointing to a fundamental role of the gut and microbiota in the pathogenesis and development of PD.

In a recent paper, Magistrelli et al. showed that in peripheral blood mononuclear cells (PMBCs) of a cohort of PD patients, probiotics were able to modulate the production of cytokines toward an anti-inflammatory profile and to reduce the production of reactive oxygen species (ROS) [15]. The clinical effects of probiotics have also been explored in other pathological conditions. Tankou et al. administered a probiotic mixture containing viable lyophilized bacteria including four strains of Lactobacillus and three strains of Bifidobacterium in nine multiple sclerosis patients, whose peripheral immune system shifted towards an anti-inflammatory profile, with an inverse tendency after administration discontinuation [16]. These results were confirmed by the same group in a different trial [17].

In the light of this evidence, we designed a pilot randomised placebo-controlled clinical trial to test the potential of probiotics therapy in modulating the inflammatory phenotype, to possibly normalise the gut-brain-microbiota axis, decreasing peripheral inflammation to finally affect disease progression in a cohort of PD patients. Feasibility objectives will be evaluated in the pilot clinical trial, including recruitment, acceptance, and dropout rates. The measurement of possible changes in intracellular and extracellular cytokine levels (IFN-γ, TNF-α, IL-4, and IL-10), ROS production, transcriptional factors mRNA levels, and lymphocyte subpopulations will be used for the selection of appropriate primary outcomes for the following main trial.

#### Objectives

The aim of this pilot study protocol is to assess the feasibility of a randomised controlled trial to assess the effects of a 3-month probiotics therapy in a cohort of Parkinson’s disease patients. Specific feasibility objectives will be assessed to define the feasibility of the proposed clinical trial, including recruitment, acceptance and dropout rate, and outcome identification, as listed in the following Table 1.

**Table 1 Tab1:** Feasibility objectives

**Objective**	**Description**
Recruitment rate	The number of identified eligible subjects in a given amount of time, at the proposed clinical setting.
Acceptance rate	The fraction of identified eligible subjects who will be willing to participate in the proposed clinical trial.
Dropout rate and safety	Dropout rate will be reported as the fraction of enrolled subjects who will be dropped from the study for any reason. Reported reasons for subject drop-out will be recorded and analysed to confirm safety for both the treatment and placebo administration to enrolled subjects.
Primary outcome identification and sample size estimate	The primary outcome for the future main clinical trial will be identified among significant immune profile changes detected in the pilot trial. Data from the pilot trial will also be used to estimate an appropriate sample size for the main trial.
Secondary outcomes identification	Collected data in the pilot trial will be used to identify promising secondary outcome measures.

Data collected during this pilot study will include the following assessments to evaluate possible outcome measures for the definitive randomised controlled trial:1) Cytokines production (IFN-γ, TNF-α, IL-4, IL-10), as already tested in vitro, to confirm the immune-modulating potential of probiotics.2) Assessment of CD4+ and CD8+ T naïve/memory cells, CD4+ T helper subsets, CD4+ regulatory T cells, monocytes, and NK cells to test the immunomodulating effects of probiotics administration on the immune profile.3) Monitoring of motor and non-motor symptoms of PD, including gut function, and subjective quality of life during the trial period.

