#### Interventions

This is a placebo-controlled trial. The intervention group will be treated with a daily dose of probiotics, while the control group will be given identical packages containing maltodextrin only, used as a bulking agent in the probiotics’ formulation for the intervention group. In this pilot study, our aim is to assess the potential of probiotics therapy to modify the peripheral immune system profile and function in a cohort of PD subjects. In this pilot trial, the potential immunomodulating effects of probiotics will be tested. Placebo treatment was chosen as a comparator for this new approach to immunomodulation in PD.

During the enrolment visit, the medical and neurological examination will assess the need for immediate variations in medical therapy for each participant. Within 2 weeks, any therapy modification will be completed, and a baseline visit will be scheduled.

During the baseline visit (T0), physical and neurological examinations will be repeated to confirm the subject’s conditions and persistence of inclusion criteria, a baseline blood withdrawal will be performed, and all clinical evaluation scales will be completed to set baseline scores. Each participant, after the subscription of an appropriate informed consent, will be randomised and given a treatment box, containing single-dose sachets with 2.7g of powder of the allocated formulation. Patients will be instructed to take daily doses at home every morning before breakfast for 12 weeks, mixing the content of one sachet in about 125 ml of fresh water or other cold, non-carbonated drink. Participants will be instructed to keep unused or empty packaging for recollection and compliance evaluation.

Product compositions per dose (1 sachet, 2.7g) for the treatment and placebo compounds are listed in the following Table 3.

**Table 3 Tab3:** Treatment and placebo composition

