### Outcomes

#### Primary feasibility outcomes

To assess the feasibility of the proposed clinical trial, we defined different feasibility objectives, as previously listed in Table 1.

More in detail, we will evaluate the potential recruitment rate for the clinical trial by recording the number of eligible outpatients who scheduled a neurological examination in the proposed clinical setting during the pilot trial. The acceptance rate will also be evaluated, by recording the fraction of identified eligible subjects who will be willing to participate in the proposed clinical trial. Both assessments together will allow for an initial estimate of the needed duration for the main clinical trial, once an appropriate sample size will be defined based on the pilot trial results. During the pilot trial, the dropout rate will also be recorded to adjust the predicted trial duration based on the fraction of dropped-out subjects during the trial period.

Reported reasons for subject drop-out will also be recorded and further analysed to confirm the safety of both the treatment and placebo administration to enrolled subjects. Collected data during the pilot trial will be analysed to assess whether a significant variation in any recorded parameter will occur between the two trial branches. This will allow to accordingly select one or more appropriate primary outcomes for the main trial, among collected immune profile data. Secondary outcomes for the main trial will be selected in the same way, among parameters who will show a remarkable variation.

More in detail, in our previous in vitro study (Magistrelli et al., 2019), we demonstrated that probiotics modulate ROS and cytokine production by driving an anti-inflammatory profile. Therefore, we will test whether these properties are confirmed in vivo. Particularly, in our study, we want to analyse whether probiotics may modulate cytokines production, such as IFN-γ, TNF-α, IL-4, IL-10, and ROS production.

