### Sample size

The design of this pilot study is explorative and equally randomised to treatment with probiotics or placebo. Due to the exploratory nature of the proposed study, a formal sample size calculation is not strictly required [18]. In our precedent in vitro study, statistically significant results were found in a small cohort of 40 PD patients for all tested probiotic strains, with a global reduction in proinflammatory cytokines production and an increase in anti-inflammatory cytokines. Doubling this sample size, with at least 80 specimens to be collected at both T0 and T2, will allow us to correctly evaluate the feasibility of the future main study.

We thus used data from the said study to estimate sample sizes for the in vitro effect of all tested probiotic strains and a sample size of 80 subjects allows for the determination of most tested cytokines variations with an expected power greater than 80%, setting our threshold for statistical significance at 0.05.

As previously stated, the drop-out rate of this pilot study will also be recorded and used to determine an appropriate sample size increase for the main study.

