#### Adverse event reporting and harms

All potential adverse events will be recorded by clinical staff and participants will be encouraged to report any new or worsening symptom, which will timely and thoroughly be evaluated for possible correlations with the administered treatment.

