## Discussion

The involvement of the immune system in the development and progression of Parkinson’s disease makes it a promising target for a disease-modifying therapy. This clinical trial will test the ability of probiotics therapy in modulating the peripheral immune system, which in turn is expected to have beneficial effects on disease progression and patients’ quality of life. If this trial shows a potential beneficial role of probiotics in immunomodulating peripheral immunity in PD patients, a trial with a larger cohort could be designed and disease progression could be monitored over a longer period to assess the disease-modifying potential of this intervention.

The possibility to use probiotics as adjuvant therapy in Parkinson’s disease could also help in reducing necessary drugs for the treatment of disease-related symptoms such as laxatives, prokinetics, and others (with a final reduction of individual therapy undesired effects and costs). The results of this study will also point further research in a disease-modifying direction. If further research shows a potential disease-modifying effect of probiotics, treatment could be proposed to all PD patients without any specific risks and increasing the quality of life in these patients.

In our mono-centric setting and considering rigorous exclusion criteria, one possible problem will be the recruitment of a large enough number of subjects. Enrolment will therefore be proposed to all eligible subjects by clinical neurologists during routine visits and given their recorded consent to receive information about ongoing research and recruiting trials. This will help in reaching the maximum number of possible participants, while ensuring strict adherence to inclusion/exclusion criteria, since participation will be only proposed to eligible patients by their neurologist and after a thorough medical evaluation.

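### The safety objective is tied to drop-out reasons and says they will confirm safety; drop-out is a poor measure of harm here, and about 40 patients per arm can only describe safety

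*Protocol article*

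**What the plan says.** Table 1 (Objectives) has a row that combines drop-out rate and safety. It states: "Reported reasons for subject drop-out will be recorded and analysed to confirm safety for both the treatment and placebo administration to enrolled subjects". The section on primary feasibility outcomes says the same, with drop-out reasons "further analysed to confirm the safety of both the treatment and placebo administration to enrolled subjects". The statistical methods section follows this line. It reports drop-out as a number and percentage by arm, records the reasons, and uses them to enlarge the main trial. It names no adverse event summary.

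Adverse events are dealt with elsewhere. The section on adverse event reporting and harms says "All potential adverse events will be recorded by clinical staff" and has them evaluated for a possible link with treatment. The Interventions and Blinding sections also have suspected reactions reported, recorded and evaluated.

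On size and exposure, the abstract says "At least 80 patients affected by PD will be recruited and randomly allocated to either the treatment or placebo group in a 1:1 ratio", and the Interventions section says "Patients will be instructed to take daily doses at home every morning before breakfast for 12 weeks".

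The Discussion adds, in a sentence conditional on further research showing a disease-modifying effect, that "treatment could be proposed to all PD patients without any specific risks".

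**The concern.** The protocol names drop-out reasons as the variable from which safety is to be concluded, and it does so twice. That is a stated choice of measure, not a detail left open. There are two problems with it.

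First, drop-out in this trial is not a harm measure. The rules that remove patients serve other purposes, mainly to protect the immune endpoints. Some removals will have nothing to do with the product, and tolerated adverse events never enter the named analysis.

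Second, confirming is a stronger conclusion than this number of patients allows, whichever measure is used. A pilot report that follows the objective as written could state that safety was confirmed because few or no drop-outs were attributed to treatment. That statement would be carried into the planning of the main trial.

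**Working it through.** **1. What drop-out captures under the protocol's own rules**

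| Situation | Where stated | Counted as drop-out? | A harm of the product? |
|---|---|---|---|
| Antibiotic or immunomodulating therapy started | Interventions | Yes, always | Not necessarily |
| Substantial change in antiparkinsonian therapy | Eligibility criteria; Interventions | Yes, always | Not necessarily |
| Intercurrent infection or inflammatory episode | Eligibility criteria | Depends on severity and on closeness to a visit or blood draw | Possibly |
| Adverse event, patient continues | Adverse event reporting and harms (recorded) | No | Possibly |

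In the third row, two infections of equal severity may be classified differently because of the date of the blood draw. In the fourth row, the event is recorded but falls outside the analysis that the objective names.

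**2. Statements on drop-out data that do not fit together**

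- Table 1, the primary feasibility outcomes and the statistical methods: drop-out reasons are recorded, and are analysed or used.
- Plans to promote retention: data collected before drop-out are kept and used as appropriate.
- Interim analyses section: drop-outs are excluded and their related data are not collected.

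Read literally, the last statement removes data that the first two need.

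**3. What about 40 per arm can show**

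The protocol gives no figure for safety, so there is none to reproduce. Its only precision statement is that "a sample size of 80 subjects allows for the determination of most tested cytokines variations with an expected power greater than 80" per cent. That concerns cytokines, and it cannot be reproduced because no effect size or standard deviation is given.

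Inputs: at least 80 patients at 1:1 (abstract), so n = 80/2 = 40 per arm; 12 weeks of treatment (Interventions).

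Exact upper limit for the true rate after 0 events in n patients:

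- One-sided 95%: 1 − 0.05^(1/40) = 7.2%.
- Two-sided 95%: 1 − 0.025^(1/40) = 8.8%.

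If safety were judged in completers only, and drop-out were 10% (n = 36) or 20% (n = 32), the limits would be 8.0% and 8.9% one-sided, or 9.7% and 10.9% two-sided. Both drop-out rates are assumptions; the protocol gives none.

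Chance of seeing no case at all in 40 patients, (1 − p)^40, for assumed true rates p:

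- p = 1%: 67%
- p = 2%: 45%
- p = 5%: 13%

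Power to compare event rates between arms (40 per arm, two-sided 0.05, normal approximation with pooled variance under the null), for assumed rates:

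- 5% vs 10%: 13%
- 5% vs 20%: 53%
- 5% vs 30%: 85%

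**4. What is lost by counting drop-outs instead of events**

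Assume an adverse event with a true rate of 10%, of which a share s leads to drop-out.

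- At least one event among 40, if all events are counted: 1 − 0.90^40 = 98.5%.
- At least one event-related drop-out, s = 10%: 1 − (1 − 0.01)^40 = 33%.
- At least one event-related drop-out, s = 50%: 1 − (1 − 0.05)^40 = 87%.

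The rate and the shares are illustrative. The direction does not depend on them: unless every event leads to drop-out, counting drop-outs is less sensitive.

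**The case against.** The strongest reply is that the protocol does not neglect adverse events. Four sections provide for recording or evaluating them or for monitoring safety per patient: Interventions, Blinding, the data monitoring committee section, and adverse event reporting. Bowel and other non-motor symptoms are also scored in both arms with several scales. Table 1 says that drop-out reasons are analysed for safety; it does not say that nothing else will be. Event categories, the safety population and interval methods are commonly left to a full protocol or analysis plan, which are not shown here. This stands as far as it goes. A reader might infer that safety data come from drop-outs alone, and the text does not support that. The absence of a detailed adverse event plan is not held against the article. What remains is that the stated objective names the weaker measure and is nowhere linked to the better data.

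A reader might also take the Discussion phrase about risk as this trial's intended conclusion. It is not. It is a conditional outlook, nothing connects it to the drop-out analysis, and Table 1 limits the safety aim to enrolled subjects. The condition in that sentence concerns efficacy only, however, so the absence of risk is asserted without support.

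Nor can one infer that everything about drop-outs is lost, since the retention section keeps what was collected before drop-out. The defect there is a contradiction between sections.

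Finally, the zero-event limits apply to any trial of this size and contradict no stated figure. That is true, and it is why the objection is to the verb *confirm* and not to the sample size.

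**Conclusion.** The point holds in limited form. The safety objective rests on drop-out reasons, which under the protocol's rules include removals that are not harms and leave out adverse events in patients who continue. With about 40 per arm, even no events of a given type would leave a true rate of up to 7.2% (one-sided 95%) or 8.8% (two-sided 95%), so safety can be described but not confirmed.

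These two limits rest only on n = 40 and exact binomial limits. The completer figures, the power figures and the drop-out shares rest on assumed rates and serve as illustration.

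Severity is minor to moderate: this is a pilot, safety is part of one feasibility row, and the better data are already to be recorded.

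**What to change.** - In Table 1 and in the section on primary feasibility outcomes, replace confirming safety with describing safety and tolerability.
- Base that objective on all adverse events recorded under the adverse event reporting section. Tabulate them by randomised arm, in all participants who took at least one sachet, with exact 95% confidence intervals. Report drop-out reasons alongside.
- Reconcile the statement in the Interim analyses section that drop-out data are not collected with Table 1, the primary feasibility outcomes, the retention section and the statistical methods.
- As a minor wording point, qualify the Discussion phrase about the absence of specific risks. This trial cannot support it, and its exclusions (among them motor fluctuations, established cognitive decline and inflammatory bowel disease) mean that it does not study all patients with the disease.

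The cost is one extra table from data already to be recorded, some rewording, and a less favourable safety statement. Following patients for adverse events after they leave the trial would be new data collection; it is not part of this fix.
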